### Population for outcome monitoring

At least 60 children aged 1–9 in the ‘yolks’ of each cluster will be examined and have conjunctival swabs taken at 2, 12, 14, 24, 26 and 36 months during the trial to assess clinical outcomes. 324 sentinel households (6 per cluster) are visited every 2 months on a rolling basis to evaluate the efficacy of fly-control interventions using entomological measures, in line with WHO guidance for the evaluation of vector-control interventions.^24 25^ 27 households are randomly selected from the ‘Enhanced F&E’ clusters every 6–8 weeks to evaluate durability of the PTH.^24^ Three households with one or more preschool children aged 1–6 years of age within the ‘yolk’ of each cluster are randomly selected to evaluate behaviour change at 3 months and at the trial endpoint. Proxies of behaviour (presence of soap and water and presence of a functional wash station) were observed and evaluated in all ‘yolk’ households in clusters 3 months after the main intervention delivery in the first year. These observations will be repeated 3 months after the final behaviour reinforcement visit at the trial end.

### Inclusion criteria: outcome monitoring population

Children aged 1–9 years in the cluster yolk (presence of ocular *Ct* DNA and clinical outcome evaluations).Households with at least one child aged 1–6 years (behavioural outcome evaluations).Households with at least two children aged 2–9 years (sentinel and PTH durability monitoring).

### Outcome measures

#### Primary outcome

The primary outcome measure is the prevalence of ocular *Ct* detected by qPCR in children aged 1–9 years 12 months after the final MDA round (36 months). The primary comparison is between the Stronger SAFE arm (arm 4) and the standard SAFE arm (arm 1) and will be assessed using a cross-sectional randomly selected sample of at least 60 children aged 1–9 years randomly sampled from each cluster ‘yolk’. *Ct* is detected using a published *Ct*-specific qPCR assay at the Oromia Regional Health Bureau laboratory in Adama, Oromia.^26^

#### Secondary outcomes

Children in the cluster ‘yolk’ are examined for the presence of TF and have conjunctival swabs taken at each monitoring time point (at 2, 12, 14, 24, 26 and 36 months following the first MDA intervention). A key secondary outcome is TF, assessed using the WHO simplified and modified FPC (examination for the presence of follicles, papillary hypertrophy (inflammation) and conjunctival scarring) grading systems,^27 28^ and conjunctival digital photography at each time point. Further detail on the examination procedures for ocular examination and conjunctival swabbing and digital photography using previously published methods.^18^ Other secondary outcomes include facial cleanliness^29^ and quality of face-washing, fly control indicators, process indicators to measure exposure to, adherence to and recall and acceptability of F&E interventions, anthropometry and reported respiratory and diarrhoeal illness in children aged 1–60 months at 36 months and a cost analysis (online supplemental file 3).

### Statistical considerations and data analysis

#### Sample size for primary outcome

17 clusters per arm, with a sample of 60 children/cluster, gives 90% power and 95% confidence to detect an absolute difference of 4% between the control (standard SAFE) (5%) and intervention (stronger SAFE) (1%) arms, assuming a design effect of 2.5 (intracluster correlation less than 0.025, estimated from previous data^30^ and an expected cluster-level *Ct* prevalence range 0%–14%). This would also provide good power for other pairwise comparisons by arm, and at different time points. The sample size considerations for key secondary outcomes are included in online supplemental file 3.

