#### Secondary analyses

The secondary outcome of TF prevalence will be analysed in exactly the same manner as the primary outcome, except that we will adjust for baseline TF prevalence rather than *Ct*. The effectiveness of each intervention on *Ct* prevalence will be assessed separately, first comparing each trial arm with the control separately (accounting for the matching in comparing the F&E arms, by adjusting for matched pair in stage (1) then using a factorial-style approach (comparing arms 1 and 2 with arms 3 and 4 and comparing arms 1 and 3 with arms 2 and 4). The same two-stage approach employed for the primary comparison (with additional adjustment for the analysis of each intervention for the other in the factorial-style analysis) will be used.

Primary analysis of behavioural outcomes will be conducted on an ITT basis to assess whether the intervention was effective as delivered. Analysis will be adjusted for baseline levels of behaviour. Planned subgroup analysis will be done according to water access, level of education and socioeconomic status. If intervention reach is suboptimal or variable across clusters, per-protocol analyses will be performed to assess whether the intervention succeeded in changing behaviour among those directly exposed to it and subgroup analysis comparing intervention outcomes according to level of intervention exposure will also be performed. The two-stage approach will be followed as above.^23^ The costs of all aspects of the intervention will be tabulated for use in a cost analysis.

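### The stated good power for other pairwise comparisons does not follow from the design: a single-component arm between 1% and 5% cannot be well powered against both arm 1 and arm 4, and for other time points the statement is unsupported

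*Protocol article*

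**What the plan says.** The sample size section of the protocol article makes one calculation: "17 clusters per arm, with a sample of 60 children/cluster, gives 90% power and 95% confidence" for a 4-point difference "between the control (standard SAFE) (5%) and intervention (stronger SAFE) (1%) arms". It assumes a design effect of 2.5, with an intracluster correlation (ICC) below 0.025. The next sentence extends the result: "This would also provide good power for other pairwise comparisons by arm, and at different time points". No prevalence, difference or power is given for any of those further comparisons. Sample size for key secondary outcomes is referred to a supplement that is not shown.

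The section on secondary analyses then plans to assess each intervention on *Ct* prevalence, "first comparing each trial arm with the control separately". F&E comparisons are adjusted for matched pair, because the two clusters of a zone share an antibiotic allocation. A factorial-style analysis of the two margins follows.

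**The concern.** A design sized at about 90% for a 4-point difference has little power to spare. Arms 2 and 3 each carry one component of the package. If each component contributes something and neither does harm, their prevalences lie between the 1% and 5% used for arms 4 and 1. Every contrast that involves one of them is then smaller than 4 points.

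What is at stake is interpretation. The article's stated aim is evidence for programme managers and policy-makers. A reader told that power was good could take a non-significant arm 2 or arm 3 result as evidence that enhanced F&E or enhanced antibiotic adds nothing, when the comparison may have had little chance of showing a real effect.

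**Working it through.** **Inputs from the article:** 17 clusters per arm, 60 children per cluster (1,020 per arm), design effect 2.5, 5% in arm 1, 1% in arm 4. Two-sided 5% is inferred from the stated 95% confidence. The analysis is taken as an unpaired t-test on cluster summaries, without baseline adjustment. The prevalence p in arm 2 or 3 is not stated, so it is left free between 1% and 5%.

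**Formula:** SE² = [p₀(1−p₀) + p₁(1−p₁)] × 2.5 / 1,020; noncentrality = |p₀ − p₁| / SE; power from the noncentral t on 32 df (critical value 2.037).

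**1. The article's own figure.** 5% v 1%: SE² = (0.0475 + 0.0099) × 2.5 / 1,020 = 0.0001407, SE = 0.01186, noncentrality = 0.04 / 0.01186 = 3.37, power 90.5%. A z-test on the effective sample of 1,020 / 2.5 = 408 per arm gives 91.9%. The stated 90% reproduces. Solving for exactly 90% against a 5% control gives 1.03%.

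**2. A single-component arm at any p between the anchors.**
- 80% power against arm 1 (5%) needs p ≤ 1.45%.
- 80% power against arm 4 (1%) needs p ≥ 4.2%.
- No p meets both. The two powers are equal at p = 2.64%, where each is 40%. For any other p, one of the two is lower.

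This applies to arms 2 and 3 alike. So at least two of the five other pairwise comparisons have about 40% power or less, whatever p is.

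**3. Illustrations at assumed prevalences.**

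| Contrast | Power |
|---|---|
| 5% v 2% | 62% |
| 5% v 2.24% (equal ratio effects, √(0.05 × 0.01)) | 54% |
| 5% v 3% (equal additive effects) | 29% |
| 3% v 1% | 51% |
| 2% v 1% | 21% |

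**4. Kinder assumptions for the ceiling in step 2.**
- Pair matching. Arms 1 and 2 share zones, as do arms 3 and 4, so each single-component arm has one matched and one unmatched contrast. With an assumed between-cluster pair correlation of 0.3–0.7 and a paired t on 16 df for the matched contrast, the ceiling is 42–48%.
- Lower ICC. With an assumed ICC of 0.015, the design effect is 1 + 59 × 0.015 = 1.885 and the ceiling is about 50%.
- Constant between-cluster coefficient of variation k. From the ICC, k = √(0.0254 × 0.95 / 0.05) = 0.69. With variance [p₀(1−p₀) + p₁(1−p₁)] / 60 + k²(p₀² + p₁²) per cluster pair, 16 in place of 17 clusters and a normal test, the ceiling is again about 50%.

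**5. Factorial margins (34 v 34 clusters, 66 df).** Additive effects give (5 + 3)/2 = 4% v (3 + 1)/2 = 2%: 65%. Equal ratio effects give 3.62% v 1.62%: 70%.

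**6. Other time points.** The article gives no expected prevalence before 36 months. Applying the same 80% relative reduction to assumed control prevalences for arm 4 v arm 1: 2% v 0.4% gives 53%, 3% v 0.6% gives 71%, 10% v 2% gives 99.7%.

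**The case against.** The strongest reply has five parts.

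- **No stated effect.** The article gives no prevalence for arms 2 and 3, so any single power figure for them is the reader's assumption. This stands. A reader might infer that single-component power is roughly 20–60% on the trial's own assumptions. The document does not support that: only the sample size, the design effect and the two anchors are the trial's. If one component carried nearly the whole effect, its contrast with control would have 80–90% power. Step 2 avoids the problem, because it needs only that p lies between the anchors.
- **Only comparisons with control are listed.** The secondary analyses name each arm against control, not against arm 4. But the power sentence covers other pairwise comparisons without that limit. Even with control alone, arms 2 and 3 would both have 80% power only if each reached about 1.45% by itself, leaving at most 0.45 points for the combination to add.
- **The planned analysis is more efficient.** Pair adjustment can lift one matched contrast well above the unpaired figure (5% v 2.24% reaches 59–73% at pair correlation 0.3–0.7). The factorial margins reach 65–70%, and baseline adjustment may add power of a size not given. This narrows the point, but a component's unmatched contrast stays low and the factorial margins are not pairwise comparisons.
- **Time points.** A reader might infer that the claim fails at other surveys too. That is not shown. Kebeles were chosen for high TF and had had no MDA since 2018, so control prevalence at some surveys could exceed 5%, and power would then be high.
- **Harm is speculative.** The comparisons are already labelled secondary, the planned method yields risk differences with confidence intervals, and nothing says a null result will be read as no effect. This is fair, and it is why the remedy is one of wording.

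Nor is this a detail that an article leaves to the full protocol or analysis plan: it is asserted as a property of the design.

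**Conclusion.** The point holds in a limited form. The 90% for arm 4 v arm 1 is correct. The extension to other pairwise comparisons is not delivered at 36 months. For any single-component prevalence between 1% and 5%, at least one of that arm's contrasts with arms 1 and 4 has about 40% power or less, or at most about 42–50% under the more favourable assumptions on matching, ICC or between-cluster variation. The premises are the article's sample size, design effect and anchors, a two-sided 5% test, and a single component that leaves prevalence between the anchors. The figures at 2%, 2.24% and 3% are illustrations, not the trial's assumptions. For other time points the sentence is unsupported: power depends on control prevalence, which is not given, and could be about 53% or over 99%.

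**What to change.** Replace the sentence with wording such as:

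> Power is about 90% for arm 4 v arm 1 at 5% v 1%. A single-component arm must reach about 1.4% for 80% power against control; at 2–3% power is about 62–29%. Power at other time points depends on control prevalence.

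Add that the other pairwise comparisons will be interpreted from their estimates and confidence intervals, and that a non-significant result will not be read as no effect. If the authors hold expected prevalences for arms 2 and 3 or for the earlier surveys, they should state them with the resulting power, allowing for pair matching where it applies.

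The primary outcome survey was completed in August 2024 with laboratory work ongoing, so the sample size cannot change, but the rule for interpretation can still be fixed before results are known. The cost is a less favourable stated figure and one interpretive sentence. No additional participants or data are needed.

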#### Data collection and management

Census, cluster and risk factor surveys, clinical examination and entomological data are collected on mobile devices using custom-designed Open Data Kit forms. Electronic forms are encrypted on submission to a Higher Education and Research Act 2017-compliant secure server at London School of Hygiene & Tropical Medicine (LSHTM). These are uploaded as a relational database and will be downloaded for data cleaning and analysis using restricted access encryption keys. Data can be monitored in real time via the secure server. Paper forms are kept in limited-access locked storage at the trial site office during the trial and scanned for electronic storage thereafter. Data are deidentified, except for consent and MDA record forms, and will be held for a minimum of 7 years, including LSHTM electronic repositories, for which access to deidentified data can be requested. The trial protocol and statistical code will be open access.

#### Data analysis

CONSORT guidelines for analysing and reporting cluster randomised controlled trials will be followed.^31^ A flow chart will show all potentially eligible participants for the primary outcome survey performed at 36 months, and any reasons for exclusion. The number of participants assessed per cluster per arm will be shown, along with number with outcome data. The age and gender characteristics of survey participants will be summarised by arm.

#### Primary analysis

The primary analysis will be a comparison between the control arm (standard SAFE (arm 1)) and the arm receiving both enhanced F&E and enhanced antibiotic (stronger SAFE (Arm 4)). Primary analyses will be by intention to treat (ITT), with clusters/participants analysed according to the arm to which they were randomised with adjustment for baseline *Ct* prevalence.

The intervention effect on *Ct* prevalence will be estimated as a risk difference and 95% CI, estimated using a two-stage approach and adjusted for baseline prevalence of *Ct*. First a logistic regression will be fitted with baseline cluster *Ct* prevalence as an exposure and presence of *Ct* at end line as the outcome. The residuals of this regression will be used in an unpaired t-test to obtain the adjusted risk difference and the associated CI in a two-stage approach recommended by Hayes & Moulton.^23^

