### Study setting

The study is being conducted in rural communities in Shashemane Rural, Shalla and Siraro districts (*woreda*) in West Arsi, in the Oromia Region of Ethiopia. This is an arid trachoma-endemic region predominantly inhabited by Afan Oromo people. Kebeles are administrative units within each *woreda* comprising approximately 5000 people. Kebeles are subdivided into three *zones*, which are further divided into garees. Each garee includes approximately 30 households. Kebeles with a high prevalence of trachomatous inflammation-follicular (TF) in children aged 1–9 years, identified by the Global Trachoma Mapping Project and subsequent recent trachoma screening surveys, were purposively selected. MDA with azithromycin has been given annually in this region since 2016. Prior to the trial intervention MDA had not been given since 2018, in part due to restrictions imposed during the COVID-19 pandemic in 2020. In the trial, each cluster includes 2–3 garees (approximately 90 households). The ‘yolk’ includes 50 households in the centre of the cluster, from which the outcome population is selected.

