### Randomisation and assignment of interventions

This study involves 68 clusters, with 17 allocated to each trial arm. MDA takes place at the zone level, to ensure an adequate treatment buffer zone between clusters, however, the household-level F&E intervention was anticipated to be too intensive to deliver to such a large area within the context of the trial, so a two-stage approach to randomisation was taken. First, 34 zones (within kebeles) were selected based on having a high prevalence of TF in children aged 1–9 years during screening surveys. Within each zone two clusters were identified; a cluster comprises 2–3 garees (approximately 90 households collectively). The 34 zones were randomly assigned to receive either standard or enhanced antibiotic (with 17 zones receiving each option), and randomisation was restricted to ensure balance between arms in terms of TF prevalence and geographical location. The two clusters within each zone were then randomised to either standard or enhanced F&E. The randomisation sequence was generated by the trial statistician using Stata V.17.

Additionally, clusters receiving enhanced antibiotic will have a buffer zone comprising the zone of the kebele around the two clusters in that arm. Standard SAFE (including standard antibiotic) will be implemented by the national trachoma elimination programme in all settlements in surrounding buffer zones with the additional aim of minimising spillover effects (online supplemental file 2).

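### Zone allocation was restricted on TF prevalence and location, but the primary analysis adjusts only for baseline Ct; its CI is conservative to the extent that these factors predict endline Ct beyond baseline Ct

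*Protocol article*

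**What the plan says.** **Design.** Under Randomisation and assignment of interventions, 34 zones were split 17 and 17 between standard and enhanced antibiotic, and "randomisation was restricted to ensure balance between arms in terms of TF prevalence and geographical location". Then "The two clusters within each zone were then randomised to either standard or enhanced F&E". Location is not defined further; Study setting names "Shashemane Rural, Shalla and Siraro districts".

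**Primary analysis.** The analysis is by intention to treat, with "clusters/participants analysed according to the arm to which they were randomised with adjustment for baseline" *Ct* prevalence. The risk difference between arms 4 and 1 is "estimated using a two-stage approach and adjusted for baseline prevalence of" *Ct*. Stage 1: "First a logistic regression will be fitted with baseline cluster" *Ct* prevalence as the only covariate. Stage 2: "The residuals of this regression will be used in an unpaired t-test to obtain the adjusted risk difference and the associated CI". Neither TF prevalence nor location enters.

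**Secondary analyses.** The TF outcome is handled in the same way, with baseline TF in place of baseline *Ct*. For the F&E comparisons the matched pair is adjusted for in stage 1.

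**The concern.** Each zone holds one standard-F&E and one enhanced-F&E cluster and receives a single antibiotic arm. An arm 1 cluster and an arm 4 cluster therefore never share a zone, and the zone-level restriction bears directly on the primary contrast.

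Balancing a prognostic factor by design takes its contribution out of the true variance of the arm difference. A t-test on residuals that still contain that factor counts it as random error. The interval is then wider than the design warrants, and the test rejects less often than its nominal level.

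The plan carries one design constraint, the within-zone pairing, into stage 1, but not the other. What is at stake is precision in a comparison of 17 clusters with 17.

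**Working it through.** **1. The plan's own figure.** Sample size for primary outcome states: "17 clusters per arm, with a sample of 60 children/cluster, gives 90% power and 95% confidence to detect an absolute difference of 4" percentage points, 5% v 1%, with a design effect of 2.5.
- Effective number per arm = 17 × 60 / 2.5 = 408.
- SE = √[(0.05 × 0.95 + 0.01 × 0.99) / 408] = 0.01186, or 1.186 points.
- Non-centrality = 0.04 / 0.01186 = 3.372.
- Power = 0.905 by noncentral t on 32 df, and 0.919 to 0.921 by the normal approximation. The stated 90% reproduces.
- CI half-width = 2.037 × 1.186 = 2.42 points.

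**2. Effect of adding the restriction factors.** Let R² be the share of residual cluster-level variance, after baseline *Ct*, that TF and location explain. The document does not give it, so the range is an assumption.
- Excess width of the planned CI = 1/√(1 − R²) − 1.
- True type I error of the planned test = 2[1 − Φ(1.96/√(1 − R²))].
- Power after adjustment: noncentral t with non-centrality 3.372/√(1 − R²) on 28 df, that is 32 less four cluster-level terms (baseline *Ct*, zone TF, two location indicators).

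| R² (assumed) | Excess width | Type I error of planned test | Adjusted half-width, points | Power after adjustment |
|---|---|---|---|---|
| 0 | 0% | 5.0% | 2.43 | 0.902 |
| 0.05 | 2.6% | 4.4% | 2.37 | 0.916 |
| 0.10 | 5.4% | 3.9% | 2.31 | 0.929 |
| 0.20 | 11.8% | 2.8% | 2.17 | 0.953 |

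**3. Cost if the factors add nothing.** Critical t is 2.048 on 28 df and 2.037 on 32 df; 2.048/2.037 = 1.006 before rounding, so about 0.6% in width. This is slightly generous to the planned model, which would itself have 31 df if its one covariate were counted.

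**4. Why these are upper limits.** The formulas remove the whole R² share, which assumes perfect balance on both factors. The article gives no tolerance for the restriction, and balance was set over zones while the contrast uses one cluster per zone. In addition, R² is a share of total cluster-level variance. With a design effect of 2.5, roughly 1/2.5 = 40% of that is sampling noise within clusters, which no zone-level factor explains. An R² of 0.20 therefore needs about 0.20/0.60 = one third of the true between-cluster variance.

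**5. Simulation.** Restricted allocation of 34 zones under the null was simulated with 1,500 runs per scenario (three locations, mean prevalence about 3%, baseline *Ct* measured without error). Coverage of the planned *Ct*-only 95% interval was:
- 95.1% when TF and location add nothing;
- 95.8 to 95.9% when each adds 5 to 10% of latent cluster variance;
- 97.3% at 20% each;
- 97.7% at 20% (TF) and 30% (location), with a weaker TF–*Ct* correlation.

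With TF and two location indicators added, coverage was 94.0 to 95.1%. That version reduced the df of the critical value but not the divisor of the residual variance. Reducing the divisor as well widens the interval by √(32/28) = 1.069.

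**The case against.** The strongest reply is that baseline *Ct* is the outcome's own baseline value. TF is a clinical sign of the same disease, and zones were chosen for high TF, which narrows its range. Baseline *Ct* may already carry most of what the restriction balanced. One pre-specified covariate is also a parsimonious choice with 34 clusters and about 1,020 × 5% + 1,020 × 1% = 61 expected infections, only about 10 of them in arm 4. This stands as a reason to keep the effect conditional and the covariate set small. It does not explain why the factors used in the allocation were left out.

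Four stronger readings are tempting, and the document supports none of them.
- A reader might infer that the interval is too wide as a matter of fact. That needs a residual association which the article does not report; without one, simulated coverage is nominal.
- A reader might infer that the primary result is biased or its type I error inflated. The direction is the opposite: the planned test is nominal or conservative.
- A reader might infer that the trial has no power in reserve. The sample size takes no stated credit for baseline adjustment, takes the intracluster correlation as below 0.025, and samples at least 60 children per cluster.
- A reader might infer that every comparison needs the extra terms. Zone-level TF and location are constant within a zone, hence collinear with the pair terms in the within-zone F&E comparisons. The TF outcome already adjusts for baseline TF.

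**Conclusion.** The mismatch between the restricted allocation and the primary adjustment set is real and stands in the current text. Its consequence is a possible loss of precision. On the assumed range of 5 to 20% of residual cluster-level variance, the planned interval is at most about 3 to 12% too wide, and adjustment would lift power from about 90% to at most about 92 to 95%. With no residual association nothing is lost under the plan, and adding the terms would cost about 0.6% in width. These limits rest on the design inputs (5% v 1%, design effect 2.5), on perfect balance of the restricted factors, and on an R² that the document does not supply. The balance of cost and gain favours adjustment.

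**What to change.** Before results are unmasked, specify for the arm 4 v arm 1 analysis of *Ct*:
- Stage 1 includes, beside baseline *Ct* prevalence, the zone TF prevalence used in the restriction (one continuous term) and the location factor actually used (district, if that was the factor). Keep the set to these.
- Stage 2 df are reduced by the number of cluster-level covariates, in the residual variance as well as in the critical value.
- The *Ct*-only model is reported as a sensitivity analysis.

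Use the same terms in the other between-zone comparisons: arm 3 v arm 1 and the antibiotic contrast of the factorial-style analysis. For the TF outcome in these comparisons, add location only. Leave the terms out wherever matched-pair terms are fitted.

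The cost is a short, dated change to the analysis plan and a few degrees of freedom. The data were needed for the allocation, so they should already be held. Timing matters: Trial status reports the endline survey completed in August 2024 with laboratory work ongoing, so the change should be documented as made blind to results. If that is no longer possible, keep the *Ct*-only model as primary, state why, and report the fuller model as a sensitivity analysis.
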